To explore potential mediators of change, we augment the GAIN-Q3 with two brief measures of parental monitoring [89] and communication [90] (completed by both the parent and adolescent), as well as an in vivo parent-adolescent interaction task [91, 92]. The self-report measures have demonstrated good internal consistency and have correlated well with adolescent involvement in risky behavior, adolescent maladjustment, and family discord [89, 90], while the in vivo task has shown high inter-rater reliability [69]. These parenting measures will only be completed by those parents with have primary custody of their adolescent. If a parent loses custody post-discharge, parenting measures will not be administered (treating parent data as missing).

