### Data analysis plan

All 60 parents will be included in statistical analyses consistent with an intent-to-treat (ITT) model. Prior to the main analyses, descriptive statistics will be run on key variables to examine distributional properties, identify outliers, and transform variables as needed. The two treatment conditions will be compared on baseline demographic and clinical variables using basic two-group independent sample t-tests. Using a *p* < .05 criterion, significant pre-existing baseline differences between conditions on any variables will be controlled in subsequent analyses.

GAIN-Q3 data will be entered into the GAIN’s proprietary software, which offers instant error checks and validation reports to prevent missing data. Other forms will be entered directly into study laptops using REDCap (Research Electronic Data Capture), a secure web-based application, to reduce missing data and entry errors. Attrition analyses will compare follow-up completers and non-completers on baseline clinical and demographic variables to determine if they differ systematically. If no systematic differences are found between completers and non-completers, then missing data will be estimated using multiple imputation methods with five datasets, an approach that has been shown to generate unbiased estimates when data are missing at random or missing completely at random [93].

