#### Secondary outcomes: adolescent variables

Secondary outcomes include adolescent substance use and associated high risk behaviors (i.e., sexual risk-behavior, truancy, and criminal involvement). Analyses will compare trajectories of use over the post-discharge period, controlling for baseline status as a covariate. For each dependent variable, separate repeated measures Analysis of Covariance will test the influence of condition, controlling for the following covariates: baseline status on the dependent variable, baseline differences between groups, and any mental health or substance use treatment received over the follow-up period. The effect of PW dosage on each dependent variable will be calculated and partial eta squared (η2) will be used to estimate the proportion of variance caused by PW. The primary analytical goal will be to provide measures of association and 95% confidence intervals to reveal the effect size of PW on each dependent variable.

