#### Sample size and power

The study will recruit 60 participants for the randomized trial. Estimating that 15–20% may be lost to follow-up, there will likely be 50 participants with complete parent-adolescent data. We will use these participants to make judgments regarding feasibility and acceptability. Effect size estimates in prior PW studies have ranged from small to very large; the only study conducted among adolescent substance users found small to medium effects, but unlike this application, that study did not offer in-person support or an online parent board (supports that may contribute to larger effect sizes). Furthermore, even small effects, if obtained by delivering content electronically via a highly scalable platform that can reach large numbers of parents, can have significant public health implications. Despite issues with effect size stability in small samples [99], a small to medium effect paired with high levels of feasibility and acceptability would therefore be an indication that the adapted PW intervention should be tested in a larger trial. Based on the detected effect size, post hoc power analyses will be conducted to determine the number of parents required for a fully powered trial. For instance, for power of .8, a small effect size (d = .3) would require a sample of 175 per group, while a medium effect size (d = .5) would require a much smaller sample of 64 per group.

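### Multiple imputation is conditional on completers and non-completers not differing, which reverses the plan's own missing-at-random reasoning and leaves no stated method when they do differ

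*Protocol article*

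**What the plan says.** All references are to the protocol article.

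- **Data analysis plan, population:** "All 60 parents will be included in statistical analyses consistent with an intent-to-treat (ITT) model".
- **Data analysis plan, attrition check:** "Attrition analyses will compare follow-up completers and non-completers on baseline clinical and demographic variables to determine if they differ systematically".
- **Data analysis plan, consequence of the check:** "If no systematic differences are found between completers and non-completers, then missing data will be estimated using multiple imputation methods with five datasets". The reason given is that imputation is "an approach that has been shown to generate unbiased estimates when data are missing at random or missing completely at random". Nothing is said about what follows if differences are found.
- **Secondary outcomes:** for each outcome, "separate repeated measures Analysis of Covariance will test the influence of condition". The covariates are the outcome's own baseline value, baseline differences between the arms, and treatment received during follow-up.
- **Putative mediators:** the same type of model, controlling for treatment received. Latent growth models will also be attempted for both sets of analyses.
- **Sample size and power:** "Estimating that 15–20% may be lost to follow-up, there will likely be 50 participants with complete parent-adolescent data".
- **Assessments:** parenting measures are also set to missing when a parent loses custody after discharge, so the mediators have a further source of missing data.

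**The concern.** The rule turns imputation on when attrition looks unrelated to baseline and, read as written, leaves it off when attrition looks related to baseline. The reasoning that supports imputation runs the other way. A baseline difference between completers and non-completers is evidence that data are not missing completely at random. It also identifies the variables that could make missing at random plausible once they are in the model. If no such difference exists, completers resemble the full sample on what was measured, and omitting the others costs mainly precision.

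At stake are the effect-size estimates and confidence intervals that the article calls the main analytical goal of the secondary analyses, and the mediator estimates. The Sample size section uses the detected effect to judge whether a larger trial is warranted and how large it should be. The method behind that estimate should not hinge on a preliminary comparison that points the wrong way.

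**Working it through.** **1. The plan's own figures.** Loss of 15–20% from 60 leaves 60 × 0.85 = 51 to 60 × 0.80 = 48 dyads, so about 50 complete and 10 incomplete reproduces.

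**2. The rule against its justification.**

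| Attrition comparison | What it suggests | What the article provides |
|---|---|---|
| No baseline difference | Consistent with missing completely at random on measured variables; complete-case analysis does least harm | Multiple imputation, five datasets |
| Baseline difference | Not missing completely at random; may be missing at random given those variables, where imputation helps most | No method named |

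The stated justification covers both rows, but the rule applies it only to the first. In the second row nothing explains how all 60 enter the analysis. Repeated measures ANCOVA in its usual form omits a dyad with a missing visit.

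**3. Reliability of the comparison as a switch.** The article states no test or threshold for attrition; I assume a two-sided t-test at .05. With group sizes m and 60 − m, power comes from the noncentral t with 58 df and noncentrality d × √[m(60 − m)/60]. At 10 v 50 the multiplier is √(500/60) = 2.887.

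| Lost v complete | d = 0.3 | d = 0.5 | d = 0.8 |
|---|---|---|---|
| 9 v 51 | 13% | 28% | 59% |
| 10 v 50 | 14% | 29% | 62% |
| 12 v 48 | 15% | 33% | 68% |

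With k independent baseline variables and no true difference, the chance of at least one significant result is 1 − 0.95^k: 23% for k = 5, 40% for k = 10 and 64% for k = 20. The number of variables is not stated, hence the range.

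**4. Possible bias in the treatment contrast.** These simulations use assumed settings, not figures from the article.

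- *Dropout related to baseline severity in one arm only* (n = 60, true difference 0.40 SD, severity–outcome correlation 0.6). Complete cases without severity gave 0.30, complete cases adjusted for severity 0.40, and imputation using severity 0.40. The comparison found a difference in 37% of runs. Imputing when no difference was found and otherwise using unadjusted complete cases gave 0.36.
- *Dropout related to severity equally in both arms.* Complete cases and imputation both gave 0.40 for the contrast.
- *No true effect, about 17% dropout driven by severity in PW+ only, complete-case ANCOVA omitting severity.* The bias was 0.06 SD in favour of PW+; including severity left 0.002.

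For scale, an unadjusted standardized difference at 25 v 25 has a standard error of √(2/25) = 0.28, so 0.06 is roughly a fifth of one standard error.

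**5. Do the planned covariates remove it?** Only in part. For substance-use outcomes, the outcome's own baseline value largely captures severity. For truancy, sexual risk and legal involvement, substance-use severity enters only if it differs significantly between arms. That is unlikely, because the urn randomization balances on it. The mediator model lists only treatment received, apart from any between-arm baseline differences carried forward under the general rule.

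**The case against.** **The plan does not say that cases are dropped.** This stands. A reader might infer that the plan reverts to completers when differences are found. The article names no fallback and commits to all 60 parents, so complete-case analysis is only the usual default of the named model. An article may also leave a fallback to a fuller plan. The reversed condition, however, is stated here, and a fuller plan that followed it would inherit the error.

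**Other parts of the plan may protect the estimate.** Partly stands. Adjustment for the baseline value of the outcome removes the simulated bias where that value is what drives dropout. Latent growth models could use incomplete cases, but the article only undertakes to attempt them and notes that convergence is difficult in a small sample.

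**Low power makes the rule less harmful.** Partly stands. A missed difference means that imputation goes ahead, which is the benign outcome. The article also ties its .05 criterion to differences between arms, not to attrition. What remains is that the choice of method depends on a noisy comparison that can also trip by chance.

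**Withholding imputation costs about 10% in standard error.** A reader might infer this from √(60/50) = 1.095, but it does not hold. That ratio compares 50 dyads with 60 fully observed, not with 60 partly imputed. In a simulation with about 17% lost to all follow-up and an assumed baseline correlation of 0.6, the standard errors were 0.207 (full data), 0.230 (complete-case ANCOVA) and 0.231 (20 imputations). Imputation cannot restore outcomes never observed; dyads with partial follow-up could contribute something, which was not computed.

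**Five imputations are too few.** Not pressed. Taking the fraction of missing information as 0.17, relative efficiency is 1/(1 + 0.17/5) = 0.97.

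**Conclusion.** The concern holds as an error in the stated rule. The condition contradicts the missing-at-random justification in the same sentence, and the all-60 commitment lacks a stated method whenever completers and non-completers differ. This conclusion needs no simulation.

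The numerical consequence is less certain. Bias in the treatment contrast requires three things together: a fallback to complete cases, dropout that depends on a baseline variable differently by arm, and that variable being outside the model. Under assumed settings of that kind the bias was 0.06 SD with an ANCOVA omitting severity, and close to zero once severity was included. The unreliability of the switch (29% power at d = 0.5; 40% chance of a false signal with ten variables) rests on the assumed two-sided .05 test and independent variables.

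Severity is should-fix. The affected results are secondary effect sizes and mediator estimates in a pilot; this ANCOVA does not test the primary feasibility and acceptability outcomes.

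**What to change.** - Delete the condition on the attrition comparison.
- Analyse all 60 dyads in every case, either by multiple imputation or by a likelihood-based mixed model. Include arm, baseline and all observed follow-up outcomes, and the baseline predictors of dropout.
- Keep the attrition comparison, but use it to choose those predictors, not to decide whether to impute. Judge them by size of difference and relevance to the outcome as well as by p-value.
- A sensitivity analysis for data not missing at random would be a useful addition, but the correction does not depend on it.

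The cost is a few sentences in the analysis plan and minor programming. Sample size, visits and data collection do not change.

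### Where multiple imputation is used, fixing it at five datasets leaves avoidable seed-to-seed noise in the secondary and mediator effect estimates

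*Protocol article*

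**What the plan says.** The Data analysis plan of the protocol article commits to an intent-to-treat analysis: "All 60 parents will be included in statistical analyses consistent with an intent-to-treat (ITT) model". It then compares follow-up completers with non-completers at baseline and sets a condition: "If no systematic differences are found between completers and non-completers". Under that condition the method is fixed: "missing data will be estimated using multiple imputation methods with five datasets". The supporting argument is that multiple imputation is unbiased when data are missing at random or completely at random. The number of datasets is not argued for separately.

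Under Sample size and power: "The study will recruit 60 participants for the randomized trial". The same section adds: "Estimating that 15–20% may be lost to follow-up, there will likely be 50 participants with complete parent-adolescent data".

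For the adolescent outcomes, "separate repeated measures Analysis of Covariance will test the influence of condition". That section also states its aim, quoted here without its last word: "The primary analytical goal will be to provide measures of association and 95% confidence intervals to reveal the effect size of PW on each dependent". The effect found is then carried forward: "post hoc power analyses will be conducted to determine the number of parents required for a fully powered trial".

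**The concern.** Multiple imputation draws the missing values at random, so a pooled result depends partly on the seed. The fewer the datasets, the larger that dependence. The stated justification, unbiasedness, holds for any number of imputations and so does not support five in particular. Five is a stated choice, so this is not a detail left to a fuller document.

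The plan's main product for the adolescent outcomes is an effect size with its 95% confidence interval. At stake is reproducibility: two analysts who follow the plan on the same data could report somewhat different effects and interval widths for the secondary and mediator outcomes, without either departing from the protocol.

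**Working it through.** **Inputs from the protocol article.** 60 randomised; 15–20% lost; all 60 analysed; five imputations; d = .3 needs 175 per group and d = .5 needs 64 per group at power .8.

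**Assumptions, not in the document.** 30 dyads per arm; two-sided 5% level; baseline–outcome correlation 0.5; within-person correlation 0.6 where several visits are used; normal-model imputation; dropout as described in step 3.

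**1. The plan's own figures reproduce.** 60 × 0.85 = 51 and 60 × 0.80 = 48, so about 50 complete. With n per group = 2(1.96 + 0.84)²/d² = 15.7/d², d = .3 gives 174.4, hence 175. For d = .5 the formula gives 63, and the t-test solution is 63.8, hence 64.

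**2. Seed noise by Rubin's rules.** Let W be the within-imputation variance, B the between-imputation variance and m the number of datasets. The seed-to-seed SD of the pooled estimate is √(B/m). Relative to the standard error √(W + B), this is √(FMI/m), where FMI = B/(W + B) is the fraction of missing information. Relative efficiency is 1/(1 + FMI/m).

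| FMI | Noise/SE, m = 5 | Relative efficiency, m = 5 | Noise/SE, m = 50 | Noise/SE, m = 100 |
|---|---|---|---|---|
| 0.11 | 0.148 | 0.978 | 0.047 | 0.033 |
| 0.15 | 0.173 | 0.971 | 0.055 | 0.039 |
| 0.20 | 0.200 | 0.962 | 0.063 | 0.045 |

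**3. Simulation, re-imputing the same data with different seeds at 15–20% loss.**

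- Setting A: three visits, monotone dropout (dropouts keep their earlier visits), ANCOVA of the visit mean. FMI is 0.11–0.15.
- Setting B: one follow-up visit, values missing completely at random, baseline-adjusted ANCOVA. FMI is about 0.15–0.20.

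| Setting | m | Seed SD of effect (SD units) | Variation in CI half-width (CV) |
|---|---|---|---|
| A | 5 | 0.028–0.032 | 5.5–7.4% |
| A | 50 | 0.008–0.010 | 1.4–1.7% |
| B | 5 | 0.043–0.052 | 9–12% |
| B | 50 | 0.014–0.017 | 2–3% |
| B | 100 | 0.010–0.012 | 1.4–1.8% |

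In setting A the simulated noise is 0.143–0.158 of the SE at m = 5 and 0.044–0.051 at m = 50. In setting B, with true d of .3 or .5, the p < .05 verdict went the minority way in more than 5% of seeds for about 21–43% of datasets at m = 5, against about 3–8% at m = 100.

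**4. Set against sampling error.** Setting A implies an SE of about 0.20 (0.028/0.143 = 0.196; 0.032/0.158 = 0.203). An estimate of 0.30 then has a 95% interval of 0.30 ± 1.96 × 0.20, that is −0.09 to 0.69. The seed alone contributes about ±1.96 × 0.03 = ±0.06. In next-trial terms, ±0.06 spans 15.7/0.36² = 121 to 15.7/0.24² = 273 per group. The sampling interval spans 15.7/0.69² = 33 per group to no finite upper limit, because it includes zero.

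**5. Imputations needed for noise of at most 5% of the SE.** m = FMI/0.05² = 400 × FMI, which is 44, 60 and 80 for FMI 0.11, 0.15 and 0.20.

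**The case against.** Five imputations is a workable number. It introduces no bias, and the efficiency loss is 2–4%. Rubin's total variance contains the B/m term, so the reported interval already allows for the finite number of datasets. All of this stands. The nominal coverage is not in question; what five leaves is a result that moves with the seed.

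The scope is also narrow. The primary outcomes (enrollment, attendance, logins, withdrawal, satisfaction) do not depend on the imputation. Only the secondary and mediator analyses do, and the article itself calls the mediator work underpowered. Imputation is also conditional on the attrition comparison. That branch is a realistic one, however. With about 10 non-completers against 50 completers, a single baseline comparison has 80% power only for a difference of about 2.80 × √(1/10 + 1/50) = 0.97 SD, although testing many variables raises the chance that one differs.

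A reader might infer that the seed would seriously mis-size the next trial, citing 121 to 273 per group. The arithmetic is right, but the documents do not support that as the harm: step 4 shows that sampling error moves the figure far more at any m. The article also acknowledges unstable effect sizes in small samples, and its go-forward criterion is a broad effect band paired with feasibility and acceptability. Nor can one infer that the estimates or intervals would be invalid.

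Finally, the exact magnitudes rest on assumed correlations and dropout patterns, and settings A and B differ noticeably. That stands too, so the size is given as a range.

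**Conclusion.** The point holds as a minor one. Where imputation is used, five datasets leave seed noise of roughly 0.15–0.20 of the standard error, about 0.03–0.05 SD units, with interval half-widths varying by about 5–12%. This assumes 15–20% loss in 60 dyads, correlations of 0.5–0.6, and one to three visits.

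The direction does not depend on these assumptions. At FMI 0.10 the noise is still 0.14 of the SE. If visit-level or custody-related gaps raised FMI to 0.3–0.4, it would be 0.24–0.28 of the SE, with half-widths varying by 16–22%.

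The issue is avoidable irreproducibility in secondary and mediator results. Sampling error cannot be reduced without more families, whereas this component can be nearly removed by computing alone. It is best labelled a free improvement.

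**What to change.** In the Data analysis plan, replace five imputed datasets with at least 50, preferably 100, and record the seed. Add that the number will be raised if the Monte Carlo error of any effect estimate exceeds about 5% of its standard error. Fifty meets that limit only at the lower end of the plausible FMI range, while 100 meets it throughout 0.11–0.20, which is why 100 is preferable.

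The cost is a short wording change and some computing time. No visit, measure or procedure is affected.

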#### Primary outcomes: feasibility and acceptability

In the open trial and randomized controlled pilot trial, feasibility will be examined via enrollment rates (>80%) and indicators of parental engagement, with the following preliminary targets: attendance of >1 coaching sessions pre-discharge and >1 sessions post-discharge for >75% of parents, and online usage patterns of 2+ PW logins, 2+ parent board logins, and 1+ h logged in for >75% of parents. Criteria for acceptability include withdrawal rates (<20%), satisfaction ratings (>80% of items on the CSQ rated “agree” or “strongly agree”) and positive feedback from exit interviews with parents and therapists. Criteria will be finalized based on parent and staff feedback in Phase 1.

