### Overview of adaptations to Parenting Wisely tested in this protocol

This protocol examines three adaptations to the PW online model based on qualitative pilot data from 13 parents (7 parents of females, 6 parents of males), 11 adolescents (5 females, 6 males) in residential treatment, and three residential treatment staff (see Table 1 for summary of themes) that were collected as part of a larger qualitative study [66, 67]. First, based on qualitative data indicating that parents did not want to lose the “human element” of treatment, we offer parents up to four in-person coaching sessions. The first two sessions are offered while the adolescent is receiving residential treatment, the time parents described as easiest to attend sessions, in order to capitalize upon parental involvement with the residential treatment program. Second, in response to feedback that parents wanted convenient access to an expert and to other parents post-discharge, parents will receive access to an expert-facilitated online message board. Finally, in order to reinforce usage of PW and the online parent board, parents will receive two text messages weekly containing links to videos of parenting skills, messages of encouragement, and links to the online message board. Such supports are designed to sustain parental engagement, reinforce important parenting skills, and provide easier access to a treatment provider during a time when adolescents are at high risk of negative outcomes, but parents reported it was especially difficult to attend in-person sessions.

**Table 1 Tab1:** Qualitative themes about parenting interventions revealed in pilot data collection with 13 parents, 11 adolescents, and 3 residential staff

Theme	Group	Findings
Parent only sessions	Parent	Parents wanted more (and not fewer) “parent only” sessions
		Parents wanted “parent only” sessions incorporated into existing visits/obligations when possible
	Staff	Residential staff described typical “parent only” sessions as focused on case management
Parenting skills	Parent	Parents were interested in learning new ways to manage their teen’s behavior
		When asked to rate their interest in receiving a parenting skills intervention, all but one parent gave the highest possible rating (very interested)
	Adolescents	Adolescents thought their parents would benefit from skills in the areas of stress management, communication, and conflict reduction

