	Staff	Residential staff felt that parents most needed help with monitoring and communication
Timing	Parents	Parents described a mismatch between when it was easiest to attend sessions (while the teen was in residential) and when sessions were typically offered (immediately post-discharge)
		Parents stated a preference for fewer in-person sessions post-discharge
	Staff	Residential staff estimated that at least 2/3 of parents attended sessions while the teen was in treatment, but that fewer than 1/3 attended post-discharge sessions
Computer	Parents	Parents unanimously expressed comfort using computers or smartphones
		Virtually all parents reported looking for information about their teen’s treatment via the internet
		Multiple parents said they wished they could connect with an expert and other parents online
Delivery	Parents	Parents liked the idea of technology as an add-on but didn’t want to lose the “human element”
		Parents rank ordered different delivery options for a parenting intervention: parents most preferred mixed (in-person + computer) support and least preferred computer only
	Staff	Residential staff had a strong preference for a mixed (in-person + computer) approach over computer only

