## Methods

### Timing of key protocol elements

Table 2 depicts the timing of key protocol elements including enrollment, allocation (in the randomized trial), intervention, and assessments. Two issues related to the timing of protocol components bear mention. First, key procedures (i.e., consent, baseline assessment, randomization, intervention) are conducted immediately after the adolescent’s admission to residential treatment. We start the protocol immediately instead of waiting until after discharge, due to qualitative pilot data (see Table 1) indicating that parents viewed the post-discharge period as overwhelming, and that parents had concerns about their ability to schedule face-to-face sessions during this period. Starting immediately after admission also capitalizes upon a critical intervention window while the teen is in residential treatment. Second, the open trial has one follow-up assessment at 6-weeks post-discharge that focuses on feasibility and acceptability, while the pilot randomized trial has a longer follow-up assessment schedule of 6-, 12-, and 24-weeks post-discharge focused on preliminary effectiveness. Prior studies by members of our team [68, 69], have suggested that brief interventions have their strongest effect between baseline and 24 week follow-up, with significantly less change over subsequent assessments. Having three follow-up assessments during the first 24 weeks post-discharge will serve to elucidate the change that is likely to occur immediately following treatment.

**Table 2 Tab2:** Timing of enrollment, intervention, and assessment activities

Timepoint	Enrollment	Allocation	Residential treatment		Post-discharge period		
	−t1	0	~2 week stay	Discharge	+6 weeks	+12 weeks	+24 weeks
*Enrollment*							
Informed consent/assent	X						
Allocation		X					
*Intervention*							
Standard care			X	X	(Optional)		
PW+ elements							
Coaching (up to 4 sessions)			X	X	X		
Computer program			X	X	X	X	
Text messages					X	X	
Parent online message board					X	X	
*Assessment*							
Primary outcomes: feasibility and acceptability			X	X	X	X	
Secondary outcomes: adolescent outcomes	X				X	X	X
Putative mediators	X				X	X	X

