### Residential center

Evaluation of the PW+ intervention will occur at the only acute residential community SUD treatment program in Rhode Island. The facility contains 16 beds and is located about 20 min outside the state capital in a suburban area. It recently affiliated with the local hospital, but continues to operate as an independent community-based program. Average length of stay is 6–10 days. About five adolescents are admitted per week on average, which equates to approximately 260 admissions per year. Based on past year census data, about 30% of adolescents at the residential treatment center are racial/ethnic minorities, with Hispanic (about 20%) and African-American (about 10%) being the most commonly represented minority groups. There is approximately even representation of male and female adolescents. In the pilot qualitative sample, median household income was $30,000, with an extremely wide range from $18,000 to over $200,000.

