#### Individual coaching sessions

Individual coaching sessions are designed to individually tailor the PW skills to each parent’s presenting concerns. The in-person coaching sessions correspond with four of the PW vignettes: substance use, limit setting, parental monitoring, and parental communication. The initial session is 60–75 min and consists of three sections: (1) rationale for parenting skills, (2) review of PW substance use module (in session), and (3) practice applying the skill to a current problem. Subsequent sessions follow the same outline and last 45–60 min, with active use of the PW program comprising about half the session. If parents introduce problems/complaints about their adolescent, the coach will first provide validation and then discuss how to apply a pertinent PW skill. Following discharge, the coach will also direct the parent to use the online parent board for additional support.

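### Under the four-session cap, the preliminary coaching target (>1 session before and >1 after discharge) can be met only by parents who attend all four sessions, so it can be missed despite very good attendance

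*Protocol article*

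**What the plan says.** Feasibility and acceptability are the primary outcomes (Specific aim 1). Under Primary outcomes: feasibility and acceptability, the engagement targets for both the open trial and the randomized pilot include "attendance of >1 coaching sessions pre-discharge and >1 sessions post-discharge for >75% of parents". The same sentence writes its online-usage minima differently: 2+ logins to PW, 2+ to the parent board, and 1+ hour logged in. The targets are called preliminary, and the paragraph ends by leaving the final criteria to Phase 1 feedback.

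The amount of coaching is fixed elsewhere. The Overview of adaptations says "we offer parents up to four in-person coaching sessions" and adds: "The first two sessions are offered while the adolescent is receiving residential treatment". Table 2 repeats the cap of four. Under Individual coaching sessions, "The in-person coaching sessions correspond with four of the PW vignettes".

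On attendance in current practice, Table 1 reports an estimate by residential staff that "at least 2/3 of parents attended sessions while the teen was in treatment, but that fewer than 1/3 attended post-discharge sessions".

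**The concern.** Read literally, >1 means at least two. Required in both periods under a cap of four, it turns the maximum offered into the minimum needed to count as engaged. A parent who attends three of four sessions counts the same as one who attends none.

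Three features of the article suggest that this was not intended. The offer is worded as a maximum. The other minima in the sentence use the plus notation, so a parallel minimum of two would have been written 2+; >1 could be a slip for at least 1. And the program was built around the difficulty of post-discharge attendance, yet this line asks for complete post-discharge attendance from more than 75% of parents.

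What is at stake is how a primary outcome is read. Sample size and power makes high feasibility and acceptability, together with a small to medium effect, the indication for a larger trial. A threshold that can be missed at over 90% attendance gives a misleading reading on one component of that judgment. If the problem is noticed only after attendance data exist, a correction will look like a reaction to the result.

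**Working it through.** **Inputs from the article.** Target: >1 before and >1 after discharge, in >75% of parents. Cap: 4 sessions, the first 2 before discharge. Phase 2: 60 dyads. Phase 1: 10 dyads, all receiving PW+. Withdrawal criterion: <20%.

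**Assumptions.** Equal arms, so 30 PW+ parents (no allocation ratio is stated). The same attendance probability p at every session. Within-parent correlation (ICC) of 0, 0.3 or 1, since the article gives no value.

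The article derives no figure from this target, so there is none to reproduce.

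**Step 1: which patterns qualify.** Let a and b be the sessions attended before and after discharge, with a + b ≤ 4, a ≥ 2 and b ≥ 2. The only solution is (2, 2). This follows from the cap alone.

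**Step 2: the count needed.** 0.75 × 30 = 22.5, so at least 23 of 30. In Phase 1, 0.75 × 10 = 7.5, so at least 8 of 10.

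**Step 3: a miss with high attendance, needing no probability model.**
- Phase 2: 22 parents attend four sessions and 8 attend three. Sessions attended: (22 × 4 + 8 × 3)/120 = 112/120 = 93.3%. Parents qualifying: 22/30 = 73.3%. Target missed.
- Phase 1: 7 attend four and 3 attend three. Sessions attended: 37/40 = 92.5%. Parents qualifying: 7/10. Target missed.

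**Step 4: chance of meeting the target.** If sessions are independent, a parent qualifies with probability p⁴. The break-even is p = 0.75^(1/4) = 0.931. With ICC 0.3, the probability of attending all four comes from a beta-binomial distribution. If attendance is all-or-none (ICC 1), it equals p. The table gives the binomial probability of at least 23 of 30, with the per-parent probability in brackets.

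| Attendance per session | Independent | ICC 0.3 | All-or-none |
|---|---|---|---|
| 80% | 0.01% (0.410) | 1.6% (0.560) | 76% (0.80) |
| 85% | 0.5% (0.522) | 13% (0.653) | 93% (0.85) |
| 90% | 14% (0.656) | 55% (0.757) | 99% (0.90) |
| 95% | 82% (0.815) | 97% (0.873) | >99.9% (0.95) |

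In Phase 1 (at least 8 of 10), 90% attendance with independent sessions gives about 27%.

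**Step 5: denominator.** Sample size and power says feasibility will be judged on the roughly 50 participants with complete data, which is about 25 in PW+ with equal arms. The target is then at least 19 of 25 (0.75 × 25 = 18.75). At 90% attendance the chance of meeting it is 19% if sessions are independent and 59% at ICC 0.3.

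**Step 6: alongside the withdrawal criterion.** If just under 20% withdraw before completing coaching and stay in the denominator, about 0.75/0.80 = 93.75% of the remaining parents must attend all four.

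**Step 7: the at-least-one reading.** With two sessions offered in each period, (1,1), (1,2), (2,1) and (2,2) all qualify. With independent sessions the per-parent probability is (1 − (1 − p)²)², and break-even is p = 1 − √(1 − √0.75) = 0.634. The chance of at least 23 of 30 is 87% at p = 70%, 99.8% at 80% and about 100% at 90%.

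**The case against.** The strongest reply is that the targets are openly preliminary. Phase 1 is a refinement phase of 10 dyads, and finalizing the criteria is one of its announced products, so the printed threshold need not be the one applied to the randomized pilot. That stands and lowers the severity. It does not remove the point: the same sentence applies the target to the open trial, no replacement is given, and opinions about the sessions are unlikely to expose a threshold that conflicts with the cap.

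A demanding target can also be defended. The article names inadequate dose as a key weakness of existing interventions, reports a dosage effect for PW modules, and gives each session its own topic; the at-least-one reading accepts half the coaching. That stands too. If full attendance is wanted, the text should say so and give a reason.

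The low probabilities depend on independent sessions. Attendance may well cluster within parents, and then 85–90% attendance can pass. The example in Step 3 does not depend on this.

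A reader might infer three stronger things that the article does not support:

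- **That PW+ would be declared infeasible on this line.** No rule says so. Feasibility is examined through enrollment and several engagement indicators.
- **That the plan could not separate poor from excellent engagement.** Table 3 records the number of sessions attended, and even the literal cut is passed about 82% of the time at 95% attendance with independent sessions.
- **That the staff estimate in Table 1 yields a chance of success.** It is an impression of the share of parents who attend sessions in current care, not a per-session probability and not PW+ data. It shows only that full post-discharge attendance is an ambitious bar.

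The different lengths of stay in Table 2 and the text do not bear on this target, which is defined by discharge and not by a number of days.

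**Conclusion.** The point holds as a matter of counting: with at most four sessions, >1 before and >1 after discharge means all four. A primary-outcome target therefore requires full uptake of an offer worded as a maximum, and it can be missed with 93.3% of sessions attended. How often that would happen is uncertain. At 90% attendance and 30 PW+ parents, the chance of passing runs from about 14% to about 99% depending on how absences cluster, and it rests on the assumed equal arms and a common attendance rate. The supportable statement is that the target can be missed despite very good attendance, not that it would be. Whether >1 is a slip or a deliberate choice cannot be settled from the article. Severity: should fix, since the targets are preliminary and are to be finalized after Phase 1.

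**What to change.** Before Phase 1 data are seen, reconcile the attendance target with the four-session cap in one of two ways:

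1. State the target as at least 1 session pre-discharge and at least 1 session post-discharge for >75% of PW+ parents, and report the share attending all four descriptively.
2. If full attendance is intended, write all four sessions and justify the 75%, given the staff estimate in Table 1 and the withdrawal rate accepted under acceptability.

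The cost is one line of wording and no new data, because session counts are already collected. The downside of the first option is a less demanding target than the literal text; the descriptive report of full attendance keeps that information visible.
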